**Study arms**

Two arms

**(i) Standard of care arm**: participants will receive 12 weeks of sofosbuvir/velpatasvir combination

**(ii) Intervention arm**: participants will receive 8 weeks of sofosbuvir/velpatasvir combination

**Study end points**

The study will end if any of the following end point have been achieved by the study participant

1. Twelve weeks of follow-up completed after treatment completion
2. Death/lost to follow-up at any time from enrolment in study to completion of 12 weeks of follow-up
3. Detectable HCV RNA at any time point after completion of 8 or 12 weeks of DAA treatment
4. Drug discontinuation for more than two weeks at any time during treatment administration

*Follow-up of the participants*

All the participants will be followed at 4 weeks, end of treatment (8 weeks or 12 weeks of treatment) and at 12 weeks after stopping the treatment.

*Specimen collection*

A blood specimens will be collected before starting anti-HCV treatment. The blood specimens, collected before starting DAA, will be tested for HCV genotype. Genotyping will be done after the planned treatment is completed. All genotyping will be done in SGPGI only and blood specimens will be anonymised at the time of genotyping. The results of genotyping will not be revealed to the investigators till the end of the study and data are analyzed.

We will also attempt our best to collect another blood specimen after 4 weeks of anti-HCV treatment. The collected blood specimen will be transported to SGPGI for quantitative HCV RNA assay to study the rapid virological response at 4 weeks (RVR4).

*Methods for HCV genotyping*

RNA will be extracted from HCV RNA containing serum specimens using a QIAamp viral RNA Mini Kit (QIAGEN GmBH, Germany). Extracted RNA will be reverse transcribed using High-Capacity cDNA Reverse Transcription Kit (Thermo Fischer Scientific, United States) which uses the random primer scheme for initiating cDNA synthesis. For amplification and genotyping, primers specific for HCV 5’-UTR (forward primer 5’ATGGATCACTCCCCTGTGAGGAACT3’, reverse primer 5’GTCTACGAGACCTCCCGGGGCACT3’) and NS5B regions (forward primer 5’ACYACCATYATGGCNAARARYGAGGT3’, reverse primer 5’TAYCTRGTCATRGCCTCCGTGAAGRC3’) will be used. Amplification will be confirmed using 2% gel electrophoresis. The amplified product will be cleaned up to remove excess primers and unincorporated nucleotides, and will then be subjected to Sanger sequencing in both directions using the BigDye Terminator version 3.1 dye chemistry and on an ABI 3130 Genetic Analyzer (Applied Biosystems, Foster City, CA, USA). The sequences obtained in the two directions will be merged. The merged sequences for individual specimens will be aligned with each other and with those for various HCV genotypes retrieved from GenBank database [ http://www.ncbi.nlm.nih.gov/nucleotide ]). A phylogenetic tree will be constructed using MEGA 7 software and UPGMA method for the sequences obtained.

*Interim analysis*

One interim analyses of the data will be done when the 12-week follow-up of the 50% of the required sample size is completed. The results will be communicated to the institutes research committee.

*Significance/outcome of the proposed work.*

If the 8 weeks treatment is proven to be non-inferior to usual 12 weeks treatment, then a shorter treatment duration can be widely implemented in national viral hepatitis control program. A shorter course of treatment is likely to have the following benefits

- It will ease the implementation of NVHCP in the country.
- Reduced treatment duration is likely to enhance the patients’ compliance and the rate of treatment completion
- Reduced treatment duration is likely to reduce the cost of HCV treatment

**Proposed time schedule for stud**y

| **Activity** | **Time duration** | **Total time duration** |
| --- | --- | --- |
| Procurement and recruitment | 3 months | 3 months |
| Recruitment of the participants | 22 months | 25 months |
| Last follow-up of the participants | 6 months | 31 months |
| Data analysis, writing the final reports | 5 months | 36 months |

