**Objective of the study**

*Primary objective*

To compare the sustained virological response at week 12 (SVR12) after stopping 8 weeks or 12 weeks of sofosbuvir/velpatasvir in non-cirrhotic patients with chronic hepatitis C virus infection

*Secondary objective*

To compare the proportion of participants completing their planned 8 weeks or 12 weeks of treatment

*Relevance of proposed research project to public health*

If the 8 weeks treatment is proven to be non-inferior to usual 12 weeks treatment, then a shorter treatment duration can be widely implemented in national viral hepatitis control program. A shorter course of treatment is likely to have the following benefits

- Use of a single drug combination, instead of two different drugs, will ease the implementation of NVHCP in the most remote areas of the country without increasing the cost of treatment.
- Reduced treatment duration is likely to enhance the patients’ compliance to the drug treatment
- Enhanced compliance will culminate in reduced risk for drug default and drug resistance
- The results of this study could also be applied to several other Asian countries where the disease burden is high and the drug availability are similar to that in India.

*Relative importance of proposed research project in a given area (100 words)*

World Health Organization (WHO) has set the global target to eliminate the HCV by the year 2030 (1). The HCV elimination can be achieved through focus on prevention of new infection and treatment of infected persons. To achieve this target, India has recently launched a nationwide, public funded “National Viral Hepatitis Control Program (NVHCP)”.

In present era, HCV is treated with oral drugs which are safe and highly effective. Several treatment regimens are approved for HCV treatment. All the DAA regimes, which are available in India, has to be given for 12 weeks.

One of the major bottle-neck in successful HCV treatment is “12 weeks duration” of treatment. Long-duration of treatment poses logistic issues of maintaining the uninterrupted drug supply by the treatment provider and poor drug compliance by the patient. Hence, efforts are done to reduce the treatment duration without compromising its effectiveness.

*Applicability of your research project*

*(a) Short term*

HCV infected patients could effectively be treated with a shorter course of drugs.

*(b) Long term*

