**Flow of the participants**

[figure not shown]

*Sample size:*

We assumed the virological response in the reference group (12 weeks) is 95% and in the experiment group (8 weeks) as 90%, with a non-inferiority margin  of 5%, power 90% and level of significance 2.5%, with a one tailed alternative hypothesis. The required sample size is estimated as 400 participants in each arm. Assuming a 10% loss  to follow up, we raised the estimated sample size to 440 participants in each arm and total study size of 880.

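### The protocol contradicts itself on whether SVR12 is collected after a participant has been off drug for more than two weeks

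*Protocol*

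**What the plan says.** The primary objective is "To compare the sustained virological response at week 12 (SVR12) after stopping 8 weeks or 12 weeks of sofosbuvir/velpatasvir" (Protocol, Objective of the study).

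The section Study end points opens with "The study will end if any of the following end point have been achieved by the study participant" and lists four items. Item 1 is completed follow-up, item 2 is death or loss to follow-up, and item 3 is detectable HCV RNA after completed treatment. Item 4 is "Drug discontinuation for more than two weeks at any time during treatment administration".

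Directly below, under Follow-up of the participants, the protocol says: "All the participants will be followed at 4 weeks, end of treatment (8 weeks or 12 weeks of treatment) and at 12 weeks after stopping". No exception is made for discontinuers.

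Two other places bear on the point. The secondary objective is "To compare the proportion of participants completing their planned 8 weeks or 12 weeks of treatment". Under Significance/outcome of the proposed work, the protocol expects that "Reduced treatment duration is likely to enhance the patients’ compliance and the rate of treatment completion". It states no discontinuation rate for either arm.

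**The concern.** Item 4 is a treatment event, yet it stands beside death and loss to follow-up as a reason for a participant's study to end. Items 1 and 3 presuppose completed treatment, so item 4 is the one that applies to someone who stops early. A centre that follows it literally takes no HCV RNA sample 12 weeks after stopping. A centre that follows the sentence below it does. In an open-label trial at five centres, practice could differ between sites.

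The event is also linked to what is randomised. The 12-week arm is exposed to item 4 for four weeks longer, and the protocol itself expects better completion with 8 weeks. A 12-week participant who stops for good after week 8 has had at least the planned 8-week duration, and may be cured, but would have no SVR12 result.

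At stake is the primary comparison. An analysis plan can say how to classify participants without a result, but it cannot recover a sample that was never taken.

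**Working it through.** **The two statements side by side**

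| | Item 4, Study end points | Follow-up of the participants |
|---|---|---|
| Applies to | anyone off drug for more than two weeks during treatment | all participants |
| Consequence | the participant's study ends | visit 12 weeks after stopping treatment |
| SVR12 in a discontinuer | not collected | collected |

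Both cannot hold for the same person.

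**Inputs from the protocol.** SVR12 of 95% (12 weeks) and 90% (8 weeks), a 5-point margin, one-sided 2.5%, and 440 per arm (Sample size). The protocol has no figure of its own for the effect of discontinuation, so there is none to reproduce. The 5-point deficit serves here only as the case in which non-inferiority should be declared 2.5% of the time.

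**Assumed inputs, not in the protocol.** Stopping risks, and the cure rate in discontinuers.

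**General formulas.** Let d8 and d12 be the proportions discontinuing, q the share of discontinuers who would be cured, and c the cure rate in completers, equal in both arms for the second formula. Differences are 8-week minus 12-week. Bias is relative to SVR12 measured in everyone.

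- Counted as failures: bias = (d12 − d8) × q. It is never below zero when d12 ≥ d8, and is zero if d12 = d8 or q = 0.
- Excluded: bias = −(d12 − d8) × (c − q). It is zero if q = c, and otherwise against non-inferiority for q < c.

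With d8 = 2% and d12 = 5%:

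| q | Counted as failures | Excluded (c = 95%) |
|---|---|---|
| 0% | 0 | −2.85 points |
| 50% | +1.50 | −1.35 |
| 80% | +2.40 | −0.45 |
| 95% | +2.85 | 0 |

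**Failure branch with an equal weekly risk h in both arms.** Stoppers in weeks 1–8 are equally frequent in both arms and, if equally curable, cancel. Those in weeks 9–12 exist only in the 12-week arm and are assumed to respond like 8-week completers (90%).

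For h = 0.25%:

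1. On drug through week 8: 0.9975^8 = 98.02%. Through week 12: 0.9975^12 = 97.04%. Excess in the 12-week arm: 0.98 points.
2. Shift: 0.98 × 0.90 = +0.88 points.
3. Measured 8-week rate: 0.90 × 0.9802 = 88.22%. With a true deficit of exactly 5 points, the measured 12-week rate is 88.22 + 5 − 0.88 = 92.34%.
4. SE = √[(0.8822 × 0.1178 + 0.9234 × 0.0766)/440] = 0.0199.
5. Chance of declaring non-inferiority = Φ(0.00879/0.0199 − 1.96) = Φ(−1.52) = 6.4%, against 2.5% with no shift.

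The same steps at other assumed risks:

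| Weekly risk | Still on drug at week 12 | Shift | False non-inferiority |
|---|---|---|---|
| 0.25% | 97.0% | +0.9 points | 6% |
| 0.5% | 94.2% | +1.7 points | 12% |
| 1% | 88.6% | +3.3 points | 26% |

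**Consistency with the planned 95%.** If discontinuers are failures, 12-week SVR12 cannot exceed the proportion still on drug at week 12. A ceiling of 95% needs h no higher than 1 − 0.95^(1/12) = 0.43%. Of the three rows, only 0.25% satisfies this, unless the planned 95% refers to completers only.

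**Stopping near the end of the course.** Item 4 needs more than two weeks off drug, so stopping in the last two planned weeks may not trigger it. Taking 6 against 10 weeks at risk, the shift at 0.25% is (0.9975^6 − 0.9975^10) × 0.90 = (98.51% − 97.53%) × 0.90 = +0.88 points. It is unchanged because the four-week gap remains.

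**The case against.** The strongest reply is that the follow-up sentence covers everyone, so SVR12 is meant to be collected and item 4 is merely loose drafting. This stands in part: a reader might infer from item 4 alone that SVR12 is never measured in discontinuers, and the protocol does not support that as a settled design. But the follow-up sentence describes end of treatment as 8 or 12 weeks, which is the completers' schedule. It does not clearly override a rule that ends the study.

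Second, a reader might infer that the trial is biased towards non-inferiority. The documents do not support that without conditions. Discontinuers would have to count as failures, more would have to stop on 12 weeks, and some of them would have to be cured. The protocol states none of these as fact: better completion with 8 weeks is only expected, and no rates are given. Under exclusion the bias is nil or opposite. Which handling applies may be set out in an analysis plan that is not shown.

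Third, counting discontinuation as failure is a recognised composite definition that keeps every randomised participant in the analysis, so it would be wrong to say that the comparison necessarily loses its randomised basis. Exclusion would restrict it to a post-randomisation subset.

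Fourth, the size rests on assumed rates, and the larger figures (12% and 26%) sit badly with the planned 95%. That is correct, and they should not carry the argument.

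None of this removes the contradiction over whether the sample is taken.

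**Conclusion.** The point holds as an unreconciled contradiction about collection of the primary outcome. If item 4 is followed, SVR12 is missing because of an event to which the 12-week arm is exposed for four weeks longer.

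The consequence is conditional. In the failure branch, the illustration most compatible with the planning rate (0.25% per week in both arms, 90% cure in those stopping in weeks 9–12, 440 analysed per arm) gives about +0.9 points of a 5-point margin and about 6% false non-inferiority instead of 2.5%. Higher assumed rates give more. In the exclusion branch, the bias is nil or against non-inferiority. The protocol supports neither an unconditional direction nor a definite size. Correction before analysis still matters, because a sample not taken cannot be recovered later.

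**What to change.** Reconcile the two statements under Study end points so that item 4 does not end outcome follow-up. State that HCV RNA for SVR12 is sought in every randomised participant who has not died or withdrawn consent, whatever drug was taken, and that each is analysed in the assigned arm. Keep the interruption of more than two weeks as a recorded adherence event, which also serves the secondary objective on completion.

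This concerns outcome collection only. It changes no clinical rule on interrupting or stopping drug.

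The cost is a short protocol clarification and, for a small number of discontinuers, one visit and RNA test that the follow-up schedule already contains.

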**Retreatment of those who relapse after 8 weeks of sofosbuvir/velpatasvir combination**

All such participants will be retreated, free of cost, with 12 weeks of sofosbuvir/velpatasvir combination. Though their retreatment results will not be considered in our analysis.

